### Power and Sample Size Calculations

With 105 participants recruited per study arm and an estimated attrition of 20%, the study will be able to detect an effect size of 0.5 in any of the 3 primary outcomes using the independent 2-tailed *t* test with a power of 80% and a significance level of .017.

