**Methods:**

A multidisciplinary and multiethnic investigator team adapted MB to promote cultural and contextual fit for Arabic-speaking women. Intervention concepts were reviewed to ensure core content would be understood by Arabic-speaking women in Qatar. Subsequently, images, activities, and examples in the intervention manuals were adapted, as needed, to make the content more relevant to Arab culture. To deliver the adapted intervention, 30 Arabic-speaking individuals with mental health backgrounds were trained. The adapted intervention was subsequently pilot-tested with 10 pregnant women receiving prenatal care at Sidra Hospital in Doha. We are now conducting an RCT to examine the effectiveness of the adapted intervention. We plan to enroll 210 pregnant individuals who are Arabic-speaking, with 1:1 randomization to the MB intervention or usual prenatal care. Among the enrolled participants, a stratified subsample of 40 pregnant women with diabetes is being recruited. Data collection will take place at baseline and a 6-month follow-up. The primary outcomes are depressive and anxiety symptoms and perceived stress. Diabetes self-care is the exploratory outcome for the subsample of individuals with diabetes. Intervention implementation will be assessed via client and provider surveys during and after intervention delivery. Power and sample size were calculated using a 2-sided 5% effort rate and assumed analyses on the individual level, accounting for attrition of 20%.

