To adapt MB for use with Arab Arabic-speaking women in Qatar. Cultural and contextual adaptations were undertaken by a multidisciplinary and multiethnic research team.To conduct a small pilot study (n=10) that examines the acceptability, appropriateness, and feasibility of the adapted MB intervention when delivered to Arab Arabic-speaking women in Qatar. Pilot study findings are used to make final revisions to intervention and research protocols.To conduct a randomized controlled trial (RCT; n=210) to determine the effectiveness of the adapted MB intervention on depressive symptoms, anxiety symptoms, and perceived stress among Arab Arabic-speaking women in Qatar. Our primary hypothesis is that women receiving the adapted MB intervention will exhibit greater reductions in depressive symptoms, anxiety symptoms, and perceived stress compared to women not receiving the intervention.

A subaim is to recruit a stratified random sample of 40 women with diabetes (n=20 control group; n=20 MB intervention) and examine intervention effects on mental health outcomes as well as diabetes self-management.

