### Randomization Procedures and Intervention Conditions

#### Randomization Procedures

Stratified permuted block randomization with blocks of sizes 2 and 4 will be used to randomize consenting women into the control arm or the intervention arm in a one-to-one fashion. The stratification will be based on the diabetic status of the woman. The randomization will be done by a statistician who is not involved in recruiting patients. A randomized list was created by the biostatistician, which was later uploaded to Research Electronic Data Capture (REDCap; Vanderbilt University) [18,19], a web-based software package for data management. This allows for the lack of human involvement on the part of the research team in the assignment of a participant to a group. It also allows for the on-the-spot assignment of participants into either the control or intervention groups.

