### Data Collection Procedures and Study Assessments

The RCT includes 2 data collection time points—baseline and 6-month follow-up. We will attempt to collect 6-month assessments for intervention participants regardless of their engagement with the intervention. Participants will receive a remuneration of US $40 after completing each survey. Baseline and follow-up data will be collected and managed using REDCap. Women who do not choose to complete REDCap assessments will be contacted by phone by the research assistant to complete the assessment by phone or in person.

This study’s primary outcomes are a reduction in depressive symptoms, anxiety symptoms, and perceived stress. Secondary outcomes are closely linked with core MB content; secondary outcomes include behavioral activation, social support, mood regulation, decentering of thoughts, and MB skill use. The outcome associated with our exploratory aim is diabetes self-care. All measures have been validated in Arabic.

We will also assess various aspects of intervention implementation. We will conduct client surveys at the end of each MB module to assess clients’ perceptions of intervention acceptability and satisfaction. Each survey lasts 2-3 minutes and asks 3 questions pertaining to enjoyment with MB material, understanding of MB material, and anticipated use of MB material. Six months after a facilitator begins MB delivery with a client, the facilitator will receive a REDCap survey to report on the extent to which they covered all topics within an MB session (on average) and the extent to which clients were engaged in the MB material during intervention sessions.

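### If .017 is the decision level for each of the three primary outcomes, Holm's step-down would keep the same 5% family-wise error and gain power whenever more than one outcome truly improves

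*Protocol article*

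**What the plan says.** The protocol article has three primary outcomes: under Data Collection Procedures and Study Assessments, the "primary outcomes are a reduction in depressive symptoms, anxiety symptoms, and perceived stress". The primary hypothesis in the Introduction expects benefit on all of them: women given the intervention "will exhibit greater reductions in depressive symptoms, anxiety symptoms, and perceived stress compared to women not receiving the intervention".

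Power and Sample Size Calculations takes 105 women per arm and 20% attrition, and states that the trial can "detect an effect size of 0.5 in any of the 3 primary outcomes" by a two-tailed t test with "a power of 80% and a significance level of .017". The Abstract gives the overall rate: "Power and sample size were calculated using a 2-sided 5% effort rate" (evidently error rate).

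The Statistical Analysis section compares each primary outcome between arms by t test or Wilcoxon test, then by regression. It gives no significance threshold and no multiplicity procedure. The .017 in the sample-size sentence is the only level stated specifically for the primary outcomes.

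**The concern.** Read as a decision rule, a flat .017 judges each outcome in isolation: an outcome with P = .02 fails even if the other two are far below .017. A step-down rule makes use of the outcomes already rejected. Holm compares the smallest P with .05/3, the next with .025 and the last with .05, stopping at the first failure. It needs no ranking of the outcomes, no assumption about correlation and no extra participants.

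The stake is the trial's own hypothesis. Benefit on all three outcomes is the setting in which a flat split loses most against Holm, so the trial could miss claims that valid error control would have allowed.

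**Working it through.** **Inputs.** From the article: 105 per arm, 20% attrition, effect size d = 0.5, level .017, power 80%, 1:1 allocation, three primary outcomes, two-sided 5% overall. Assumed, because the article gives none: a common correlation between outcomes of 0.3, 0.5 or 0.7.

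**1. The plan's own figure.**
- Evaluable per arm: 105 × 0.8 = 84.
- Expected z: d × √(n/2) = 0.5 × √42 = 3.240.
- Critical value at two-sided .017: 2.387. Power = Φ(3.240 − 2.387) = Φ(0.853) = 80.3%. The exact noncentral t gives 79.6%.
- In reverse: n = 2 × (2.387 + 0.842)² / 0.5² = 83.4, so 84 per arm, and 84 / 0.8 = 105.

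The stated 80% reproduces. The split is .05/3 = .01667, rounded to .017. Three times .017 is .051, which is only a rounding matter.

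**2. Bounds on what Holm can give one outcome.** The level that an outcome finally faces is .05/3, .025 or .05.
- .05/3: Φ(3.240 − 2.394) = 80.1% (79.3% by exact t).
- .025: Φ(3.240 − 2.241) = 84.1%.
- .05: Φ(3.240 − 1.960) = 90.0%.

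Holm's power per outcome at d = 0.5 therefore lies between about 80% and 90%. Where it falls depends on how often the other two are rejected, which needs simulation.

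**3. Simulation.** Three correlated normal test statistics, 84 per arm, Holm at .05/3, .025 and .05. Power per outcome for the outcomes with a true effect of 0.5:

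| True effects | Correlation | Flat .017 | Holm |
|---|---|---|---|
| 0.5, 0.5, 0.5 | 0.3 | 80% | 87.1% |
| 0.5, 0.5, 0.5 | 0.5 | 80% | 86.5% |
| 0.5, 0.5, 0.5 | 0.7 | 80% | 85.8% |
| 0.5, 0.5, 0 | 0.3 to 0.7 | 80% | about 83% |
| 0.5, 0, 0 | 0.3 to 0.7 | 80% | 80% |

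Over correlations from 0 to 0.8 the three-effect figure runs from 88% down to 85%. The t version is about half a point lower: 86.6%, 86.0% and 85.2% at correlations 0.3, 0.5 and 0.7.

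- All three significant, all effects 0.5, correlation 0.3 / 0.5 / 0.7: 58% / 62% / 66% with the flat level, 75% / 77% / 79% with Holm.
- Effects 0.5, 0.5 and 0.3: power for the weaker outcome rises from 33% to 46-48%.
- At least one significant: essentially unchanged, because Holm's first step is Bonferroni at .05/3 (94.8% under both at correlation 0.5, t version).

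**4. Error control.** The simulated family-wise error with Holm is 3.9% to 4.9% with no real effect (correlation 0.7 to 0), at most 4.6% with one real effect and at most 4.2% with two. This agrees with the theory, under which 5% is a ceiling for any correlation.

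**The case against.** The strongest reply is that the article never says the outcomes will be judged at .017. The figure stands in the sample-size sentence only. Sizing at .05/3 is fully compatible with a Holm analysis, since it is Holm's first step and gives the guaranteed minimum power. The testing procedure may also be set in an analysis plan that is not shown. This stands, and it makes the point conditional. It does not remove it: .017 is the only level given for these outcomes, and a reader of the article would take it as the threshold.

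It is also true that Bonferroni is valid and that the power statement is right. Nothing here is an error. Nor does the Abstract's 5% contradict .017: one is the overall rate, the other its share per outcome.

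Three stronger readings are tempting and not supported:
- **That Holm raises power to 86-87% in general.** This needs a real effect of 0.5 on all three outcomes. The target of 0.5 in any of the three also covers an effect on one outcome alone, where nothing is gained.
- **That the trial will often show one clear result and two P values between .017 and .05, both of which Holm would rescue.** In simulation this pattern occurs in about 2.5-3.0% of trials with all effects 0.5, and in 1.5-2.4% with effects 0.5, 0.5 and 0.3. Holm does not always rescue the two, because its second step needs P at or below .025.
- **That closely related outcomes make the case stronger.** With all effects at 0.5, the gain per outcome shrinks as correlation rises.

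Finally, Holm has no simple matching simultaneous confidence intervals. That is a real but small drawback. The Statistical Analysis section plans mean differences with standard deviations and P values, not simultaneous intervals.

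**Conclusion.** The point holds as an efficiency improvement, on the condition that .017 is the decision rule. Under the trial's own hypothesis, with 0.5 on all three outcomes, 84 per arm and correlation 0.3 to 0.7, Holm adds about 6 to 7 percentage points of power per outcome. It adds about 13 to 17 points to the chance of succeeding on all three. In about 15-19% of such trials it changes the verdict on at least one outcome. The gain is about 3 points with two real effects and nil with one, and the chance of at least one significant outcome does not move. The correlation is an assumption, but across 0 to 0.8 the figure for three real effects stays at 85-88%. The plan's present level and power statement remain correct as they stand.

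**What to change.** State in both Statistical Analysis and Power and Sample Size Calculations that the three primary P values are ordered from smallest to largest and compared with .05/3, .025 and .05, stopping at the first that is not significant, for a two-sided family-wise error of 5%. Keep 105 per arm. Describe about 80% (79% at .0167 by exact t) as the minimum power per outcome for an effect of 0.5. Using .05/3 in place of .017 also removes the rounding excess. If the analysis plan already specifies Holm, a clarifying sentence in the sample-size section is enough.

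The rule must be fixed before outcome data are compared; adopting it after seeing P values between .017 and .05 would not be credible. The article reports 157 women enrolled by March 31, 2023, with recruitment still under way, so there was room to do this at that stage.

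The cost is a sentence in each section and no extra participants. For intervals, report the usual one for each outcome, or a 98.3% interval (1 − .05/3), and say that it does not correspond exactly to the Holm decision.

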## Results

This study is in progress. We have completed the cultural adaptation of MB as well as the pilot study of the adapted MB intervention. Recruitment for the RCT began in February 2022.

### Cultural Adaptation of MB

A multidisciplinary Arabic-speaking research team comprised of psychologists, psychiatrists, obstetricians, endocrinologists, and nurses led the adaptation process. This research team was of different Arab backgrounds, with ethnic backgrounds represented including Qataris, Egyptians, Sudanese, Omani, and Palestinians. This combination of different ethnic backgrounds helped tailor MB to ensure a diversity of Arab cultures. The research team worked from the MB facilitator and participant manuals and reviewed them to first ensure that core intervention concepts would be understood by Arab-origin, Arabic-speaking women in Qatar. Additionally, images, activities, and examples found in the manuals were reviewed and adapted, as needed, to render the content more relevant and appropriate to Arab culture. For example, mindfulness sessions were adapted to include an Islamic and spiritual perspective to introduce the mindfulness sessions to the client (eg, how to improve the relationship with God, which can help in daily life and how to practice culturally informed mindfulness practices). Examples of pleasant activities that clients could engage in were modified to include culturally appropriate examples (eg, reading from the Quran and visiting family) and address contextual differences in activities (eg, removing examples of window shopping and gardening) that are not typically performed by Arab women in Qatar.

### Pilot Study of Adapted MB

A byproduct of this project is deepening the capacity of mental health professionals in Qatar to address mental health with their perinatal clients. As such, 29 individuals fluent in Arabic were trained on the adapted MB manuals. The individuals included graduate students from the Doha Institute for Graduate Studies’ new master’s in psychology program, medical students from Weill Cornell Medicine in Qatar, PMH nurses from Hamad Medical Corporation and Primary Health Care Cooperation, and nurses from Sidra Medicine. The nomination of these trainees was performed based on their medical backgrounds, prior experience with CBT, and availability to deliver the intervention during the time frame of the research study. Training was led by the 2 multiple principal investigators ([name] and [name]). Training occurred over a full day and introduced trainees to the MB intervention’s core concepts and implementation considerations. Subsequently, each intervention session was reviewed with key considerations highlighted by the trainers. Emphasis was placed on highlighting places in the curriculum where adaptations were made to promote cultural and contextual fit. A second training was held for 14 of the individuals who completed the first training and indicated an interest in facilitating MB intervention sessions. This second training provided these 14 individuals with details on the study’s intervention and research procedures (eg, facilitator responsibilities, patient recruitment process). Training was delivered in both Arabic and English.

For the pilot study, 4 of these facilitators delivered the MB intervention to 10 pregnant individuals. The average number of sessions received was 7.0 (out of 12), and 4 individuals completed all 12 sessions. Baseline assessments were conducted to pilot procedures and measures to be used in the RCT. Client and facilitator feedback was used to modify study procedures and slightly adapt the intervention content.

### RCT Recruitment

Recruitment for the RCT began in February 2022 and is expected to be completed by December 2023. As of March 31, 2023, a total of 259 pregnant women had been consented and screened for eligibility. Of those screened, 157 were eligible and enrolled in the study.

## Discussion

This study has several notable strengths and innovations. It is the first study to our knowledge that examines the effectiveness of a postpartum depression preventive intervention with Arab women in the Middle East, including Qatar. Given the higher prevalence of postpartum depression among women in the Middle East [6], interventions aimed at preventing and treating postpartum depression need to be examined in this context. The intervention tested in this study is an adapted version of an evidence-based postpartum depression preventive intervention—MB. Several RCTs of MB have demonstrated its effectiveness in preventing postpartum depression in diverse perinatal populations in the United States. However, given the significant cultural differences between the United States and Qatar, we engaged in a process of culturally adapting the intervention before testing its effectiveness with Arab-origin, Arabic-speaking women in Qatar. This cultural adaptation is another strength of this study, as a multidisciplinary team of researchers and clinicians from different Arab backgrounds engaged in an intensive process of reviewing and adapting the MB facilitator and participant manuals to ensure their cultural and contextual fit.

Our recruitment of a stratified subsample of diabetic women enhances the potential impact of this project. It is well established that stress during pregnancy has an impact on blood glucose control [20]. Pregnant women with diabetes who receive MB are likely to exhibit reduced stress levels by learning the cognitive, behavioral, and stress management techniques taught through the intervention. As a result, we anticipate that we will observe better diabetes self-management.

Because each MB session lasts only about 20 minutes, sessions can be delivered during an existing health care visit (eg, while waiting for a prenatal care appointment). MB is also highly flexible, allowing for intervention delivery in person, by phone, or via telehealth (eg, Zoom, Microsoft Teams). The use of non-face-to-face interventions may be of particular benefit to women who struggle to attend prenatal appointments—for example, if women do not feel well, have a child who is unwell, or have difficulty accessing transportation or childcare. The use of phone or telehealth approaches allows for the intervention to be more easily delivered during very hot weather or during Ramadan—important contextual considerations for interventions delivered to women in Qatar and the Middle East.

This study is not without limitations. Although the adaptation of MB was conducted to promote cultural and contextual fit, caution will need to be used in generalizing findings beyond the sample recruited from one medical center in Doha. Our 6-month follow-up time point is also limited in its ability to examine sustained intervention effects as well as the impact of the intervention on parenting or parent-child attachment outcomes. Although the diabetic subsample is innovative, our sample size is limited for this exploratory aim.

Pregnancy and the early postpartum period are times of increased risk of mental health disorders—particularly depression and anxiety—that impact not only maternal and fetal well-being and functioning but also mother-infant attachment, parenting practices, and infant development. These time periods are opportune times for mental health interventions given that women access health care more frequently and families are often more motivated to engage in health-promoting activities to promote positive outcomes for their children. This study has the potential to add to the evidence base on postpartum depression preventive interventions broadly and will also be the first of its kind to do so among exclusively Arab women in the Middle East.

## Appendix

Multimedia Appendix 1 Peer review report by the National Priorities Research Program, Qatar National Research Fund (Qatar).

## Abbreviations

CBT: cognitive behavioral therapy
CONSORT: Consolidated Standards of Reporting Trials
EPDS: Edinburgh Postnatal Depression Scale
GAD-7: Generalized Anxiety Disorder-7
MB: Mothers and Babies
PMH: perinatal mental health
RCT: randomized controlled trial
REDCap: Research Electronic Data Capture
